### Ethics and dissemination

The protocol of this study declares that participants will be protected against invasion of privacy, and the source data will be securely filed in the Clinical Research Centre for Korean Medicine. This study has been approved by the Institutional Review Board of Pusan National University Hospital (H1404-022-017). This study will be conducted with respect for the individual participants according to the Declaration of Helsinki, the Ethical Guidelines for Korea Good Clinical Practice, and relevant laws and regulations. The results of the present study will be published in a peer-reviewed journal and reported at relevant conferences.

## Discussion

A previous study reported that there is an increasing demand for CAM, especially traditional Korean medicine (TKM), among Korean children with CP [22]. TKM, which is derived from TCM, is very different from TCM in practice and is widely used in Korea. Only a few clinical case reports have evaluated the effectiveness and safety of TKM; therefore, more data are required to provide optimal information to children with CP and their guardians.

In general in South Korea, children with cerebral palsy concurrently receive their treatments in many rehabilitation clinics and rehabilitation centres in hospitals. Although they often change medical institutions for rehabilitation therapies, conventional therapies usually last approximately 30 min per session. Therefore, if we collect information regarding the types of interventions, the number of medical institutions, and the number of sessions, we can calculate the amount or intensity of intervention to a certain degree for statistical analysis.

The aim of this study is to analyse the effectiveness, safety, and cost-effectiveness of both conventional and TKM combination treatment for children with CP. This study is designed to evaluate the effectiveness of many types of interventions, including TKM, on cerebral palsy and to compare effectiveness between groups with or without TKM. From this initiative, we will attempt to identify the gross effectiveness of interventions, and then we will try to measure the amounts of interventions that can increase outcomes by digitizing intensity, duration, and frequency. We hypothesize that TKM combination treatment for children with CP will have benefits compared with conventional therapy alone, and as such, TKM combination treatment might be promoted in the development of an advanced guideline for integrative rehabilitation. Moreover, the findings of this study might provide informative data for conducting economic evaluations and developing a future randomized controlled trial (RCT) of combination treatment for CP in South Korea.

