In Korea, children usually receive conventional treatment, including physical, occupational, or speech-language therapies, and they also have a demand for traditional Korean medicine (TKM) interventions such as acupuncture or herbal medicine. We now aim to investigate the effectiveness, safety, and cost-effectiveness of both conventional and TKM combination treatment for children with CP.

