## Methods/Design

### Study design

The study team is conducting a one-year, multi-site, prospective observational study of rehabilitation for children with CP. We are recruiting the children at two university-affiliated hospitals, one TKM hospital and three TKM clinics. The children with CP receive treatments from doctors and therapists in each clinic or centre, and one independent investigator assesses functional changes in participants and collects survey documents from their guardians or parents. We will analyse changes in the children’s functional development and health condition, the number of adverse events, and monetary resources spent for rehabilitation during this period. This design is a comparative observational study of a conventional treatment group and a TKM combination treatment group (Fig. 1).

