### Primary outcome measurement

The first primary outcome is the changes from baseline of the GMFM-66 scores at weeks 26 and 52. The GMFM-66 includes 66 items identified through Rasch analysis, which collectively best describe gross motor function in children with CP of varying abilities [15, 16]. The second primary outcome is the changes from baseline of the PEDI scores at weeks 26 and 52. The PEDI uses 217 questions to measure abilities in the three functional domains of self-care, mobility and social function [17].

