### Rationale for sample size

The sample size was determined on the basis of the primary outcome measure, GMFM-66. Using a 2-sided test, a sample size of approximately 37 children per treatment would assure 80 % power to detect a difference of at least 1.6 points (α = 0.05) assuming a standard deviation of 2.2 and dropout rate of 0.2. This mean change of 1.6 points in GMFM-66 scores was considered a clinically meaningful change in previous studies [17, 19]. We also planned the sub-group analyses considering disease severity measured by GMFCS (2 sub-groups, I-III and IV-V) and age (2 sub-groups, <3 and ≥3) heterogeneity. Therefore, a total of 300 participants will be required.

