### Statistical and analytical plans

The study will present both descriptive and comparative results of conventional treatment and TKM combination treatment. In this study, we define operationally the conventional treatment (CT) group as children who have received only PT, OT, ST, and other conventional therapies, whereas the TKM combination treatment (CT + TKM) group is defined as children who have received at least twelve sessions of any type of acupuncture or 30 days of herbal medication within a 6-month follow-up period in addition to conventional therapies. At the time of analysis, participants will be classified in the conventional or TKM combination treatment group based on the six-month or one-year follow-up information (Fig. 2).

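### The Discussion's aim of identifying the gross effectiveness of interventions cannot be met: without an untreated or developmental reference, within-group change cannot be told apart from natural development

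*Protocol article*

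**What the plan says.** The protocol article describes its structure under Study design: "This design is a comparative observational study of a conventional treatment group and a TKM combination treatment group". The Discussion goes further. It says: "This study is designed to evaluate the effectiveness of many types of interventions, including TKM", and joins to this, as a second item, the comparison of groups with and without TKM. It then adds: "we will attempt to identify the gross effectiveness of interventions", followed by a plan to measure how much intervention raises outcomes, using intensity, duration and frequency.

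Under Statistical and analytical plans, the CT group is defined as "children who have received only PT, OT, ST, and other conventional therapies". The combination group has TKM on top of conventional therapy. The same section plans:

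- a propensity-score comparison of the two groups, with age, GMFCS and treatments in the score;
- a correlation of rehabilitation intensity with functional change inside each group;
- a comparison of acupuncture with acupuncture plus herbal medication inside the combination group.

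The outcome is change over time: "The first primary outcome is the changes from baseline of the GMFM-66 scores at weeks 26 and 52", with PEDI handled in the same way. Table 1 schedules these assessments at baseline, month 6 and month 12.

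**The concern.** The extra aim concerns what the interventions achieve as such, including conventional therapy. That needs some view of how these children would have changed without them. The design offers none, yet its outcome is motor and functional change in very young children over a year. Study design itself describes the quantity studied as functional development, and the Background rests the case for early rehabilitation on the plasticity of the developing brain. Natural development is never named as a rival explanation of change.

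At stake is how the results are read. A mean rise inside a group, or a correlation of intensity with gain, could be presented as the effectiveness of conventional therapy or of TKM when some or all of it is development.

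**Working it through.** **1. What within-group change contains.** Assume effects add up. Let D be mean natural development over follow-up, C the effect of conventional therapy and T the added effect of TKM.

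- CT group: mean change = D + C.
- CT + TKM group: mean change = D′ + C′ + T.
- Difference = T + (D′ − D) + (C′ − C).

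The first line is one equation with two unknowns. D could be supplied by an untreated group, a pre-treatment slope or a reference growth curve. The article describes none of these. Table 1 has a single score before follow-up, so no earlier slope can be estimated. The baseline interview already records rehabilitation and TKM, so baseline need not precede treatment.

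In the difference, D′ − D vanishes when the groups are balanced on what drives development. Age and GMFCS are both named in the propensity score. The main contrast therefore does not share this defect.

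**2. The intensity analysis.** Write a child's change as D(age, GMFCS) + b × intensity. If b = 0, the covariance of change with intensity equals the covariance of D(age, GMFCS) with intensity. That is non-zero whenever age or severity influences both how much therapy a child receives and how fast the child develops. No adjustment for either is stated, so the correlation cannot tell b from D.

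**3. What the 1.6 points are.** Inputs from Rationale for sample size: difference 1.6, SD 2.2, two-sided α 0.05, power 80 %, dropout 0.2.

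- n per group = 2 × (1.960 + 0.842)² × 2.2² / 1.6² = 29.7, so 30 evaluable.
- With dropout: 30 / 0.8 = 37.5, so 38; or 30 × 1.2 = 36. The stated figure is about 37.
- Total: 37 × 2 groups × 4 strata = 296, against the stated 300.

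The sizing reproduces with 1.6 as a difference between groups. The justification calls it a change: "This mean change of 1.6 points in GMFM-66 scores was considered a clinically meaningful change". The two wordings should be aligned.

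**4. Illustration of size.** The documents give no growth rate, so the natural gain g is an assumption throughout.

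| Assumed g (points) | g / 1.6 |
|---|---|
| 0.5 | 31 % |
| 1.5 | 94 % |
| 3 | 188 % |

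A larger sample does not help. Take no treatment effect, SD 2.2 and a two-sided 0.05 test of within-group change, with SE = 2.2/√n and normal approximation. At n = 30 the chance of significance is 0.238, 0.702 and 0.978 for g = 0.5, 1.0 and 1.6. At n = 150 (half of 300) it is 0.795 for g = 0.5 and above 0.99 for the other two. The article does not plan such a test, so this shows only that precision makes the misreading firmer.

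**The case against.** The strongest reply is that this takes loose Discussion wording for an analysis that is not planned. Much of that reply stands:

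- A reader might infer that each group's rise will be tested and declared an effect. The documents do not support this. The planned tests are a two-sample t-test and a linear mixed model for the group comparison. No paired or one-sample test appears, and the analysis section already promises descriptive alongside comparative results.
- A reader might infer that a within-group rise would feed a guideline or a future trial. The Discussion ties the guideline to the hypothesis that combination treatment is better than conventional therapy alone, and the trial it mentions is of combination treatment.
- The Background sentence, "We now aim to investigate the effectiveness, safety, and cost-effectiveness of both conventional and TKM combination treatment for children with CP", may mean one combined regimen. It is not firm evidence of a second aim.
- That future authors would hold within-group change against 1.6 points is conjecture.
- There are contrasts between children inside the groups. The acupuncture comparison bears on adding herbal medication, though, not on conventional therapy. The intensity correlation is open to the confounding shown above.

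The reply does not supply a comparator for the aim the Discussion states. Objectives and comparator structure are matters the article fixes itself, so an unseen analysis plan would not cure the mismatch.

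**Conclusion.** The point holds in limited form. The Discussion claims more than the design can identify. Change in GMFM-66 or PEDI inside either group cannot be attributed to conventional therapy or to interventions in general, and the intensity correlation as described does not repair this.

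It would be wrong to conclude that the CT + TKM versus CT comparison fails for the same reason. Shared development cancels there, provided the groups are balanced on age and GMFCS. Nor can a positive within-group result be called likely, because that depends on a growth rate the documents do not give. The size is therefore unknown, and the figures above only illustrate a range. The sample size and the primary comparison need no change.

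**What to change.** 1. In the Discussion, limit the effectiveness aim to the adjusted CT + TKM versus CT difference and delete the aim of identifying gross effectiveness.
2. State that within-group changes in GMFM-66 and PEDI are descriptive and are not read as treatment effects. Show them by the age and GMFCS subgroups already set out in Rationale for sample size.
3. Adjust the intensity analysis for age and GMFCS and label it exploratory.
4. In Rationale for sample size, state that the 1.6-point mark applies to the between-group difference only.

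The cost is wording and slightly more analysis. Age and GMFCS are already collected, so no new data or participants are needed. The study gives up a claim it cannot support.

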## Abbreviations

ATx, acupuncture; CAM, complementary and alternative medicine; CP, cerebral palsy; CT, conventional treatment; GMFCS, Gross Motor Function Classification System; GMFM-66, Gross Motor Function Measure-66; Mx, medication; OT, occupational therapy; PEDI, Paediatric Evaluation of Disability Inventory; PT, physical therapy; QALYs, quality-adjusted life years; QOL, quality of life; RCT, randomized controlled trial; SAEs, serious adverse events; ST, speech therapy; TCM, traditional Chinese medicine; TKM, traditional Korean medicine;
